Patients are included under broad inclusion criteria: (1) diagnosis of primary colorectal cancer and (2) surgery in one of the four participating hospitals. Exclusion criteria are as follows: (1) recruiting surgeon (QoL clinician) is not available (illness, holiday, other reasons); (2) patient is misclassified in the operation schedule (no primary operation or no colorectal tumour); (3) coordinating practitioner (physician, caring for the patient) chosen by the patient refuses trial participation; (4) patient is from outside the defined study region (Bavaria, Germany: urban county of Regensburg, rural county of Neumarkt, Straubing, Straubing-Bogen, Kelheim, Schwandorf); (5) age under 18 years; (6) pregnancy; (7) patient unable to fill out the QoL questionnaire for physical, psychological, or language reasons (including dementia); or (8) patient refuses to participate in the study. To insure high external validity [20] , there will be no exclusion of elderly patients or exclusion according to tumour stage or patient sex. Furthermore, no constraints will be made according to surgical procedure or ASA score (American Society of Anesthesiologists); however, these factors will be accounted for in data analyses. External validity is also kept high by population-based inclusion of patients of urban and rural areas and by implementing the QoL pathway into routine follow-up care. Moreover, data of the cancer registry of excluded patients and other hospitals in the study region can be analysed according to medical and demographic data of patients to test representativeness of our study population. The selection of study participants is shown in Fig. 1.

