#### Health status (surgeon/CP)

The first measurement of health status is performed before discharge from the hospital. The surgeon gives information about the following demographic and medical characteristics of the patient: age, sex, marital status, children, occupation, ASA classification, tumour stage, date of surgery, surgical procedure, complications, comorbidities, (neo)adjuvant therapies, other current or planned therapies (for example, pain therapy, psychotherapy physiotherapy), CEA, preoperative symptoms, height, and weight. The type of surgery and ASA classification especially are expected to affect strongly colorectal cancer patients’ QoL [30]. These variables will be considered in data analysis, but neither specific surgical procedures nor higher ASA classifications will be excluded in order to achieve high external validity.

During follow-up the CP gives written information about health status at 3, 6, 12 and 18 months postoperatively regarding CEA, finished, current, or planned therapies, and complications. Additionally, the CP makes an assessment of the patient’s global QoL on a seven-point Likert scale.

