### Statistical analyses

Trial data are entered into a Microsoft ACCESS (version 2007) database, which is installed on a password-protected computer without physical connection to the internet. All data entered into the database are controlled by a second, independent member of the QoL Unit.

All variables will be presented using descriptive statistics (frequencies, percentages, means/standard deviations, medians/interquartile ranges, and various graphical representations). Point estimates will be accompanied by confidence intervals.

The design for the two primary endpoints is based on a method of fixed a priori ordered hypotheses [31]. Thus, the second primary endpoints will only be analysed, if the null hypothesis of the first primary endpoint can be rejected (*P* < 0.05). This design assures a global alpha of 0.05. The analyses of the primary endpoints (including both first and second primary endpoints) will be conducted using the *Χ*^2^ test (or Fisher’s exact test if the smallest expected cell value is < 5), setting the level of statistical significance at *P* < 0.05. It is not planned to use imputation to handle missing data in primary analysis.

Statistical tests regarding the secondary endpoints will also use the *P* < 0.05 significance threshold, but all secondary results will be interpreted in an exploratory manner.

Secondary analyses will start with an ANCOVA using the continuous QoL data as dependent variable and baseline QoL, comorbidity, sex, age and study site as covariates. Other secondary analyses will focus on exploratory subgroup analyses. These include the influence of different surgical procedures on QoL and the benefit these different subgroups gain from the QoL pathway. Furthermore, risk factors for diseased QoL (ASA, stoma, type of tumour (colon/rectum), age and sex) will be investigated. Tests of significance will include the Mann-Whitney *U* test, Kruskal Wallis test, *t*-test, and ANOVA or McNemar, depending on the number of groups, their independence/dependence, and the scaling of the dependent variable.

For qualitative data in the final questionnaire about patient satisfaction, a category system will be created and answers will be categorised by independent raters, so that frequencies of key categories can be quantitatively analysed by using descriptive statistics [32].

A detailed statistical analysis plan (SAP) will be written before all analyses commence.

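### The only covariate-adjusted model named, the secondary ANCOVA, omits surgical procedure and ASA class, which the protocol says elsewhere will be accounted for

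*Protocol article*

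**What the plan says.** Four sections of the protocol article bear on this.

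- **Participants and recruitment** sets no entry limits on surgical procedure or ASA score, in the interest of external validity, and adds a qualification: "however, these factors will be accounted for in data analyses".
- **Health status (surgeon/CP)** lists both among the items the surgeon reports before discharge. It says: "The type of surgery and ASA classification especially are expected to affect strongly colorectal cancer patients’ QoL". It then repeats the commitment: "These variables will be considered in data analysis, but neither specific surgical procedures nor higher ASA classifications will be excluded".
- **Statistical analyses** tests the primary endpoints with chi-square or Fisher's exact tests, without covariates. The secondary analyses open with an ANCOVA on the continuous scores, with "baseline QoL, comorbidity, sex, age and study site as covariates". Procedure returns under exploratory subgroup analyses: "These include the influence of different surgical procedures on QoL and the benefit these different subgroups gain from the QoL pathway". ASA returns in one place: "risk factors for diseased QoL (ASA, stoma, type of tumour (colon/rectum), age and sex) will be investigated". All secondary results are declared exploratory, and a detailed SAP is to be written before analysis begins.
- **Randomisation and blinding** describes a single list of 220 in blocks of 20, with no stratification by procedure or ASA.

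**The concern.** Two sections single out procedure and ASA as factors with a strong expected effect and commit the analysis to dealing with them. The section that specifies the analysis then prints a closed covariate list without either. The list is not deferred to the SAP, so a SAP that follows it inherits the omission.

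The subgroup analysis asks whether benefit differs between procedures. The risk-factor analysis asks which patients have diseased quality of life. Neither gives an overall treatment effect adjusted for these factors, and ASA enters no stated treatment comparison at all.

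At stake are the precision of the ANCOVA estimate and its protection against a chance imbalance between arms. If an imbalance is noticed later, adding the covariates then would look data-driven.

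**Working it through.** **1. The sections side by side**

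| Factor | Expected strong effect | Commitment | In the ANCOVA | Stratified | Other use |
|---|---|---|---|---|---|
| Surgical procedure | yes | yes, twice | no | not described | exploratory subgroups, including benefit by procedure |
| ASA class | yes | yes, twice | no | not described | exploratory risk factor for diseased quality of life |

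**2. The plan's own figure.** The Sample size section gives 89 per group for 25% versus 45%, with α 5% and power 80%. Two-sided, with pooled variance under the null and no continuity correction:

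n = [1.96·√(2·0.35·0.65) + 0.842·√(0.25·0.75 + 0.45·0.55)]² / 0.20² = 88.09, rounded up to 89.

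This reproduces the stated figure. It rests on an unadjusted test, so the ANCOVA covariates do not enter it.

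**3. Precision.** Let r be the share of the ANCOVA's residual variance that procedure and ASA would explain beyond the covariates already listed. The protocol gives no value, so r is an assumption shown over a range. The standard error is multiplied by √(1 − r), and the gain is worth 1/(1 − r) in patients. An ANCOVA that had 80% power would move to Φ(2.80/√(1 − r) − 1.96), where 2.80 = 1.96 + 0.84.

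| r (assumed) | SE multiplier | Worth in patients | Power, from 80% |
|---|---|---|---|
| 2% | 0.990 | 1.02 | 81% |
| 5% | 0.975 | 1.05 | 82% |
| 10% | 0.949 | 1.11 | 84% |
| 20% | 0.894 | 1.25 | 88% |

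These figures are before the cost of the added parameters. With 220 × 0.8 = 176 evaluable patients and, say, five added parameters (assumption), that cost is roughly 5/176 = 2.8% of variance. An r of about 3% is therefore near break-even.

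**4. Chance imbalance.** With 110 × 0.8 = 88 evaluable patients per arm and a factor of prevalence p (assumed), the SD of the between-arm difference is √(2p(1 − p)/88).

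- p = 20%: SD 6.0 percentage points, 95% range about ±12.
- p = 30%: SD 6.9, about ±14 (1.96 × 6.9 = 13.5).
- p = 50%: SD 7.5, about ±15.

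To turn this into an effect on the estimate, suppose the factor shifts the 12-month score by 10 points, net of the listed covariates (assumption). An imbalance of 13.5 percentage points then moves the treatment estimate by 0.135 × 10 = 1.4 points on the 0–100 scale. With a 20-point shift it moves by 2.7 points.

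**The case against.** The strongest reply is that nothing has been broken. The commitments are loosely worded and do not promise covariate adjustment. The plan does examine benefit by procedure and does study ASA as a risk factor. On a loose reading that satisfies the wording in the Health status section. It fits the firmer wording under Participants and recruitment ("these factors will be accounted for in data analyses") less well, because ASA then plays no part in any comparison of the arms.

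A second reply is that the listed covariates already do part of the work. Baseline quality of life is measured 0 to 2 days before discharge, after the operation, so it can carry part of the effect of procedure. Comorbidity and age overlap with ASA. This stands, and it is why r must be read as incremental and may be small. It does not make the two factors redundant. The protocol lists comorbidities and ASA as separate items, and it chose 12 months because stoma reversal and adjuvant therapy are often incomplete at 6 months. The course after baseline may therefore depend on procedure.

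Three stronger readings are tempting, and the protocol supports none of them.

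- A reader might infer that the primary result is compromised. It is not: the unadjusted primary tests are valid under randomisation whatever the ANCOVA contains.
- A reader might infer that the protocol ranks these two factors above all others. It expects a strong effect but does not place them above, for example, baseline quality of life. Its stated reason for broad entry is external validity, not the later adjustment.
- A reader might want the same covariates in an adjusted analysis of the binary endpoint. The protocol names no such analysis.

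**Conclusion.** The mismatch is real and can be checked by reading: the only adjusted model named leaves out two factors that the protocol says it expects to matter and will account for. It is minor. The ANCOVA is secondary and exploratory, and randomisation guards against systematic confounding.

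What is lost is some precision, about 2.5–5% of the standard error if r is 5–10%, and correction for chance imbalances that would typically move the estimate by a few points at most under the assumptions shown. Both sizes rest on assumed explained variance, prevalence and effect of the factors, none of which the protocol gives. The label is a free improvement of minor severity.

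**What to change.** Add surgical procedure and ASA class to the ANCOVA covariates in Statistical analyses and carry them into the SAP, before any analysis starts. Recruitment was still in progress and the SAP still to be written, so this can be fully prespecified. Use the values the surgeon records before discharge, and collapse rare procedure categories without looking at outcome by arm. Stoma is not named among the surgeon-recorded items, so it should not be listed as a separate covariate on the assumption that it is.

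The cost is one line of text and a few degrees of freedom out of about 176. No new data are needed, and the primary test and sample size stay as they are.

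If the sponsor meant only the subgroup and risk-factor analyses, the alternative is to say so under Participants and recruitment and under Health status. That removes the inconsistency but forgoes the gain in precision.

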## Discussion

In a complex intervention a clinical pathway with QoL diagnosis and QoL therapy has been developed, implemented, and the effectiveness has already been demonstrated for breast cancer patients. To provide the QoL pathway to other cancer patients as well, external validity needs to be extended by adapting the QoL pathway to another cancer type.

This randomised trial is the first complex intervention investigating the effectiveness of an intervention with regular measurement and treatment of QoL in colorectal cancer patients. The primary objective is to improve the QoL of the patients during follow-up care by systematic diagnosis and tailored therapy of diseased QoL. This regular screening of QoL combined with targeted therapy is supposed to support the prevention of chronic QoL deficits like fatigue or reduced emotional functioning.

Therefore, the treatment of cancer patients’ QoL needs to be just as standardised as medical therapy. This is a major strength of this study. In contrast to other interventional trials on QoL, the setting of this study is not limited to the inpatient process but encompasses especially ambulant routine follow-up care. Furthermore, the QoL pathway exceeds other approaches to improve QoL by not only measuring QoL and presenting results but also giving recommendations how to improve QoL, providing regional network structures for QoL therapy. Additionally, the trial is expected to have high external validity, for example, no exclusion of older patients, of specific tumour stages, or of patients with comorbidities. Therefore, the study has been carefully designed to reflect routine attending the recommendations in the S3-guideline. The four cancer centres responsible for patient recruitment are considered to be representative for institutions in which the QoL system is planned to be implemented in routine health care in the future. During the recruitment phase all colorectal cancer patients, surgically treated in the four hospitals, will be screened for study eligibility. We also expect a special motivation of CPs to participate in the trial because they are informed about the study by their patient’s surgeon and are implemented by an educational outreach visit. Moreover, thorough planning and a lot of preliminary work have been done in the course of the complex intervention including theory building [17, 18], modelling [5], and pilot testing.

A limitation is the complexity of the trial. As a result, it might be difficult to determine which specific facet of the intervention is responsible for an effect. Therefore, the specific QoL therapies patients receive at any time of measurement are recorded and will be investigated for effectiveness in subgroup analyses.

To disseminate study results, full text publications and presentations at conferences will be realised as well as the transfer of the results into the medical education of physicians and students. Furthermore, the randomised trial is an implementation study for colorectal cancer patients as well. The QoL system has already been implemented for patients with breast cancer in the area of Regensburg and is now implemented for colorectal cancer patients. The effectiveness of this modified QoL pathway in such a different patient population will be tested in this prospective randomised trial. In the long term, the QoL system is planned to be implemented for the whole region of Germany.

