**Methods/Design:**

The QoL pathway will be tested for colorectal cancer patients in a pragmatic randomised controlled trial. Two hundred twenty primary colorectal cancer patients, surgically treated in one of four hospitals, will be included. QoL is measured in all patients 0, 3, 6, 12, and 18 months after surgery (European Organisation for Research and Treatment of Cancer (EORTC) QLQ-C30, QLQ-CR29). In the intervention group, QoL scores are transformed into a QoL profile. This is sent to the coordinating practitioner (general practitioner, internist, or oncologist) with an expert report including treatment recommendations for QoL deficits. The control group receives routine follow-up care attending the guideline recommendations for colorectal cancer without profile or expert report. At the primary endpoint (12 months), the rates of patients with diseased QoL in both groups are compared.

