### Procedure

Written informed consent is obtained from each participant before they are included into the study. All participants (intervention and control group) repeatedly fill out a QoL questionnaire (EORTC QLQ-C30, QLQ-CR29 [23–25]) at the following times: 0 to 2 days before discharge from hospital and 3, 6, 12 and 18 months postoperatively. The first QoL measurement takes place in hospital and the further measurements (3, 6, 12, 18 months postoperatively) are carried out in the CP’s practice during follow-up. For each assessment time point participants receive a postal reminder. Guideline for colorectal cancer [26] recommends first follow-up at 6 months. Colorectal cancer patients suffer a lot of QoL deficits especially in the first months of treatment. Therefore, we decided also to measure QoL 3 months postoperatively. Feasibility of this additional measurement is expected to be good because most patients visit their CP regularly. This could be also observed in the pilot phase of the study.

Parallel to the QoL measurements, the patient’s CP provides additional information about the patient’s health status. All data are sent to the QoL Unit at the Tumour Centre Regensburg.

All patients are treated according to the follow-up regimen of S3-guideline for colorectal cancer [26]. Concomitant care is not prohibited but will be collected and considered in secondary data analysis.

Differences between the treatment of intervention group and control group patients is shown in the following section. Figure 2 gives an overview of the study flow in the two arms of the randomised trial.

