#### Intervention group

The QoL pathway for intervention group patients is shown in Fig. 3. All intervention group patients receive, in addition to routine follow-up care [26], tailored QoL diagnosis and therapy during the first 18 months after surgery. For this purpose measurements of a QoL questionnaire (EORTC QLQ-C30, QLQ-CR29 [23-25]) are transformed into a QoL profile using a computerised visualisation programme [27]. The profile consists of scales of 0 to 100 (worst to optimal QoL) comprising global QoL and 12 different dimensions considering somatic (e.g. pain), psychological (e.g. emotional functioning), and social aspects (e.g. family life) (Fig. 4). The QoL profile also takes into account the specific discomfort colorectal cancer patients suffer, for example, disability during defecation, increased bowel movement, or discomfort during urination (EORTC QLQ-CR29). A cut-off score has been constructed, which defines scores < 50 points as ‘diseased QoL’.

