### Measures

#### Quality of life (patient)

Quality of life is measured by using the validated QoL questionnaire of the European Organisation for Research and Treatment of Cancer (EORTC), consisting of a core module (EORTC QLQ-C30 [25, 28]) and a module for colorectal cancer patients (EORTC QLQ-CR29 [23, 24]). The questionnaire is a self-administration instrument with a multidimensional structure measuring QoL on a four-point Likert scale or rather on a seven-point Likert scale for the global dimension QoL. Satisfying internal consistency and good retest-reliability, as well as construct and clinical validity, have been demonstrated [24, 28, 29].

In every dimension scores are uniformly transferred to a scale from 0 (very bad QoL) to 100 (very good QoL). A cut-off score has been constructed, which defines scores < 50 points as diseased QoL. This score has been extensively discussed and accepted in the present form by consensus of a large group of clinicians [5, 6, 18].

For outcome measurement of the present randomised trial, 13 different scales have been selected according to the results of the previous randomised trial in breast cancer patients [6], the appraisal of relevance for QoL of colorectal cancer patients, and the availability of therapy options (global QoL, physical functioning, role functioning, pain, discomfort during defecation, increased bowel movement, discomfort during urination, body image, emotion, concentration/remembering, fatigue, family life/social encounters, and financial situation).

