#### Telephonic enquiries (CP)

Four weeks after the patient has filled out the QoL questionnaire, a member of the QoL Unit calls the CP by telephone and asks if anything has been done to improve the patient’s QoL. The reason for this is that in the intervention group CPs receive a QoL profile and an expert report with recommendations for improving their patients’ QoL. Therefore, whether anything has been done in response to the expert report is to be recorded by phone call. In order to ensure comparability of patients in both study arms, there are also telephonic enquiries for CPs of control group patients.

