### Primary and secondary outcomes

The first primary endpoint (1) will be the proportion of patients in both groups with diseased QoL (<50 points in at least one dimension) 12 months postoperatively. Twelve months were chosen because adjuvant therapies and stoma reversal are often not finished 6 months postoperatively.

The second primary endpoints (2), enhancing the credibility of the first primary endpoint, are the rates of patients with diseased QoL in each dimension of the profile 12 months after surgery.

The primary endpoints formulated above will be tested in the strict order (1), (2), that is, a statistical testing procedure with a priori ordered hypotheses is applied [31]. This binary primary endpoint was chosen for two reasons: (1) according to our conceptual groundwork [5, 19] 50 score points on a 0 to 100 QoL scale defines healthy versus diseased QoL, and (2) the same primary endpoint was used in our randomised trial on breast cancer patients and generated a significant difference according to our hypothesis [6].

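### Exploratory subgroups by QoL therapy received are confounded by indication and cannot show which therapy is effective

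*Protocol article*

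**What the plan says.** In the protocol article, the Discussion names the complexity of the intervention as a limitation, because "it might be difficult to determine which specific facet of the intervention is responsible for an effect". It then offers a remedy: "the specific QoL therapies patients receive at any time of measurement are recorded and will be investigated for effectiveness in subgroup analyses". No caveat follows.

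Other sections show how a patient comes to receive a therapy:

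- The Abstract (Methods/Design) says that the practitioner of an intervention patient receives the QoL profile "with an expert report including treatment recommendations for QoL deficits".
- The Measures section (Quality of life (patient)) fixes the threshold: "A cut-off score has been constructed, which defines scores < 50 points as diseased QoL". The Sample size section likewise equates having no deficit with all scores being at least 50.
- Under Telephonic enquiries (CP), the practitioner decides whether to act, and "whether anything has been done in response to the expert report is to be recorded by phone call".
- The first primary endpoint is the proportion of patients with "diseased QoL (<50 points in at least one dimension) 12 months postoperatively".

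The Statistical analyses section classes subgroup analyses and all secondary results as exploratory. It describes one adjusted model, an ANCOVA with baseline QoL, comorbidity, sex, age and site, and a list of two-group, multi-group and paired tests. A detailed SAP is announced; it is not among the documents at hand.

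**The concern.** The grouping variable, therapy received, arises after randomisation and is driven by an earlier value of the outcome. A patient below 50 at 3 or 6 months is more likely to receive a therapy. If low scores persist, that patient is also more likely to be below 50 at 12 months, whatever the therapy does. Recipients and non-recipients then differ in prognosis by construction.

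At stake is the answer to the question that the Discussion itself raises. A useless therapy can look harmful, and a useful one can look neutral or harmful. If recipients are instead compared with their own earlier scores, a useless therapy can look beneficial. This error is systematic and does not shrink with more patients.

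**Working it through.** **The plan's own figure.** The article gives no figure for the therapy analysis. Its sample size reproduces and is not in dispute. With 45% against 25% deficit-free, two-sided 5% and 80% power, n = [1.96·√(2·0.35·0.65) + 0.8416·√(0.45·0.55 + 0.25·0.75)]² / 0.20² = (1.322 + 0.555)² / 0.04 ≈ 88.1, so 89 per group. After 20% drop-out, 110 × 0.8 = 88 remain per arm.

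**Illustration 1: recipients against non-recipients, inert therapy.**

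Inputs:
- 35% deficit-free at 12 months: the midpoint of the article's 25% and 45%.
- Assumed, not in the article: 70% with a deficit at 6 months; uptake of 5% without a deficit and u with one; a bivariate normal latent score with 6-to-12-month correlation r; true therapy effect zero.

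Let f₁ and f₀ be the probabilities of being deficit-free at 12 months with and without a 6-month deficit. Then

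- recipients: (0.70·u·f₁ + 0.30·0.05·f₀) / (0.70·u + 0.30·0.05)
- non-recipients: (0.70·(1−u)·f₁ + 0.30·0.95·f₀) / (0.70·(1−u) + 0.30·0.95)

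The model gives f₁ = 0.272 and f₀ = 0.532 at r = 0.4, and f₁ = 0.226 and f₀ = 0.639 at r = 0.6. At r = 0 both are 0.35.

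Worked case, r = 0.4 and u = 0.80: recipients (0.56·0.272 + 0.015·0.532)/0.575 = 0.279; non-recipients (0.14·0.272 + 0.285·0.532)/0.425 = 0.447. The gap is 17 points.

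| r | u | Deficit-free, received | Deficit-free, not received | Apparent harm (points) |
|---|---|---|---|---|
| 0 | any | 35% | 35% | 0 |
| 0.4 | 20% | 30% | 36% | 6 |
| 0.4 | 40% | 29% | 38% | 9 |
| 0.4 | 80% | 28% | 45% | 17 |
| 0.6 | 20% | 27% | 37% | 10 |
| 0.6 | 40% | 25% | 39% | 15 |
| 0.6 | 80% | 24% | 50% | 27 |

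Setting u = 5%, so that uptake is unrelated to QoL, also gives a gap of zero. The low-uptake rows may be nearer to a single specific therapy, since the profile has 13 scales and therapy is tailored. At u = 20%, 15.5% of patients receive the therapy, about 14 of 88.

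**Illustration 2: one dimension.** Assumed: mean 65, SD 25, uptake 60% below 50 at 6 months and 5% otherwise. Entries are the percentage below 50 at 12 months, received against not received.

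| r | Inert therapy | Therapy worth +10 points |
|---|---|---|
| 0.3 | 37% vs 25% | 23% vs 25% |
| 0.5 | 44% vs 23% | 29% vs 23% |
| 0.7 | 53% vs 21% | 35% vs 21% |

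A useful therapy keeps the right sign, barely, at r = 0.3 and loses it at 0.5 and 0.7.

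**Before-after within recipients, same model, inert therapy.** The share below 50 falls from 82% at 6 months to 37%, 45% and 53% at 12 months for r = 0.3, 0.5 and 0.7. This is regression to the mean alone. McNemar's test, suited to such a comparison, is on the article's list.

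**Where the bias comes from.** Restrict the inert comparison to patients below 50 at 6 months, with uptake random among them, and it disappears: 40% vs 40%, 50% vs 50%, 62% vs 62%. If uptake within that group rises with severity, part remains: 42% vs 37%, 54% vs 44%, 67% vs 53%. Conditioning on the deficit removes most of the bias but not all of it.

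**The case against.** **These analyses are exploratory, and the primary comparison is randomised.** Both statements are true, and they limit the weight of the point. But an exploratory label warns against chance and multiplicity. It does not warn that the contrast is biased in expectation.

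**The article names no comparator and the SAP may set one.** This stands in part. The Discussion sentence is brief, and missing detail is not the finding. The finding is that the article offers groups formed by therapy received as its means of judging effectiveness. The baseline QoL in its one adjusted model is measured before discharge, so it does not capture a deficit at 3 or 6 months that prompts therapy.

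**Size and sign rest on assumptions.** This stands. Correlation, uptake and comparator are not given, so only a range is defensible. Results of the wrong sign are possible, not certain.

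**Stronger readings.** A reader might infer that the arm effect will be adjusted for care received after randomisation, because the Procedure section says "Concomitant care is not prohibited but will be collected and considered in secondary data analysis". The documents do not support that: considering such care is not a stated adjustment, and the ANCOVA covariates include no received care. A reader might also infer that therapy-level results would decide what is rolled out. The Discussion speaks of implementing the QoL system as a whole and ties no therapy to a subgroup result.

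**Conclusion.** The point holds as a limited one about an exploratory analysis. Subgroups by therapy received cannot be read as evidence of a therapy's effectiveness, because the indication for therapy and the outcome use the same cut-off on the same scales.

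Under the first set of assumptions, an inert therapy looks 6 to 17 points harmful at correlation 0.4 and 10 to 27 points at 0.6, over uptake of 20% to 80% among patients with a deficit. The bias needs both persistence of scores and uptake that depends on QoL; without either it is zero. Its direction depends on the comparator: towards harm against non-recipients, towards benefit against recipients' own earlier scores.

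**What to change.** In the Discussion and the SAP, replace the investigation of received therapies for effectiveness with a descriptive report of therapies received, by arm.

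If a therapy-level estimate is still made:
- label it observational and hypothesis-generating;
- compare only patients with the same deficit at the same visit;
- adjust for the score that triggered the recommendation;
- state that confounding by severity may remain.

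A randomised exploratory analysis may be added: for each dimension, compare the arms at 12 months among patients scoring below 50 in that dimension at discharge. That score is measured in both arms before any recommendation. The result must be stated as the effect of the whole pathway in that dimension; it does not isolate a single therapy, which this design cannot do by randomisation.

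The cost is wording and a SAP entry, since the data are already to be collected. The downside is smaller subsets and wider intervals.
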